#### Qualitative analysis

We will comprehensively explore the lived experience of participating in a community-based stroke wellness program) and community reintegration. Little is known about what community reintegration means to the person with stroke [99, 100]. An interpretive phenomenological approach will be utilized, following a constructivist paradigm [101]. Two reviewers will examine the transcripts and carry out independent, line-by-line analysis to generate initial codes, which will be finalized by consensus. Codes will then be consolidated into categories. The investigators will independently review each other’s coding of the transcripts to assure credibility. Next, we will extract quotes throughout the transcripts that correspond to the established codes and categories. Short summaries will describe the major ideas emerging from the data.

#### Cost-effectiveness analysis

The cost-effectiveness analysis will compare the incremental cost and effectiveness of the YMCA-based FIT for FUNCTION program with the standard YMCA membership for stroke survivors, from both the public healthcare payer’s perspective and the societal perspective. Effectiveness will be measured with QALY, using the utility values calculated from the EQ-5D-5L with duration. The main summary measure for the cost effectiveness analysis will be the incremental cost per QALY gained over the 24-week duration of the trial. Given that this cost-effectiveness analysis is conducted alongside the trial, non-parametric bootstrap will be used to calculate the 95% CI around the incremental cost per QALY ratio. The decision uncertainty will be presented using cost effectiveness acceptability curves, which show the probability of the intervention being cost-effective compared with the control group at specified societal willingness-to-pay for a QALY. The economic analysis will be conducted in using Statistical Analysis Software 9.2.

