#### Research questions and specific hypotheses

The proposed trial aims to answer the following research questions:Is the 12-week FIT for FUNCTION stroke program more effective than a standard YMCA membership in improving community reintegration (primary outcome) at 12 and 24 weeks?

*Hypotheses:* Participants in the FIT for FUNCTION group will demonstrate greater post-program improvement in community integration. Gains will be maintained at 24 weeks (12 weeks following program completion).2.Is the FIT for FUNCTION stroke program more effective than a standard YMCA membership in increasing levels of physical activity and improving physical functioning (walking, balance, strength), health-related QOL, cardiovascular health, and self-management at 12 and 24 weeks?

*Hypotheses:* Participants in the FIT for FUNCTION group will demonstrate greater post-program improvement in physical activity, physical functioning, health-related QOL, cardiovascular health, and self-efficacy. Gains will be maintained at 24 weeks (12 weeks following program completion).3.Is the FIT for FUNCTION program more cost-effective than a standard YMCA membership?

*Hypotheses:* Participants in the FIT for FUNCTION program will have lower direct and indirect medical costs over the 24 weeks of the trial period as evidenced by fewer hospital and physician visits, and formal and informal caregiver services. The costs associated with the FIT for FUNCTION program will be less than those for the control group. We also hypothesize that the FIT for FUNCTION program will be more effective in improving health-related QOL of participants.4.What participant characteristics are associated with degree of program response observed?

*Hypotheses:* Participants who demonstrate greater improvement in community integration (primary outcome) from the FIT for FUNCTION program will have less co-morbidities, illness severity, depressive symptoms, mobility, and cognitive impairment.

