To assess the effect of the intervention on RNLI (research question 1), physical activity levels, physical functioning, QOL, cardiovascular health, and self-management (research question 2), we will estimate group, time, and group × time interaction effects using generalized linear models for continuous variables. We will include relevant baseline variables as covariates in the analysis that differ between groups at baseline, notably time since stroke (TSS) if there is a significant between-group difference. We will also include the baseline score for the specific measure of interest. For example, for research question 1, the baseline score of the RNLI would be included as a covariate for evaluating post-program changes.Our hypothesis is that there will be reduced hospitalizations and physician visits for the intervention group compared to the control group (research question 3). Cost data are usually treated as non-parametric; therefore, a Mann–Whitney U test will be used to test relative ranks of participants between the groups on relative intervention cost.We will use prognostic indicators from participants’ profiles to determine factors associated with the greater benefit from the FIT for FUNCTION program (research question 4). These factors will be identified by expanding the models for the treatment effects on RNLI and function as the dependent variables, and using prognostic variables of co-morbidities, illness severity, depressive symptoms, mobility impairment and cognitive status, education, previous level of activity, stroke classification, and interactions involving age and gender, as independent variables in the regression models.

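### The planned 95% CI around the cost-per-QALY ratio cannot tell a dominant programme from a dominated one, and the trial's own hypothesis lies where this matters (minor; the acceptability curve is unaffected)

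*Protocol article*

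**What the plan says.** Research question 3 in the protocol article asks: "Is the FIT for FUNCTION program more cost-effective than a standard YMCA membership". The hypotheses under it fix a direction for both components. On cost: "The costs associated with the FIT for FUNCTION program will be less than those for the control group". On effect: "We also hypothesize that the FIT for FUNCTION program will be more effective in improving health-related QOL of participants".

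The Cost-effectiveness analysis section then sets the estimand and its interval. "The main summary measure for the cost effectiveness analysis will be the incremental cost per QALY gained over the 24-week duration of the trial", and "non-parametric bootstrap will be used to calculate the 95% CI around the incremental cost per QALY ratio". No rule is given for negative ratios or for replicates that fall in different quadrants of the cost-effectiveness plane.

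The next sentence adds a second output: "The decision uncertainty will be presented using cost effectiveness acceptability curves", which give "the probability of the intervention being cost-effective compared with the control group at specified societal willingness-to-pay for a QALY". Elsewhere, in the Analyses section, costs are compared by rank: "a Mann–Whitney U test will be used to test relative ranks of participants between the groups on relative intervention cost". The Objectives section lists cost-effectiveness as a tertiary objective.

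**The concern.** A ratio of two differences loses the sign of each. When the cost difference and the QALY difference have opposite signs, the ratio is negative whether the programme is cheaper and better (dominant) or dearer and worse (dominated). Within that region its size is not an ordering either: a larger saving makes the ratio more negative, but so does a smaller QALY gain. An interval for the ratio inherits both problems. The hypothesis places the expected result in exactly this region.

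There is a second, conditional problem. A bootstrap replicate whose QALY difference is close to zero gives a ratio of very large size and either sign. If an appreciable share of replicates crosses zero, these values set the percentile limits.

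At stake is the readability of the main economic figure. If the hypothesis is right, the main figure would be a negative ratio whose interval may run from large negative to large positive values. The rest of the article does not clearly supply what the ratio hides: the rank test yields no mean cost difference, and no interval is stated for incremental cost or incremental QALYs.

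**Working it through.** The plan states no numerical result for the economic analysis, so there is no figure to reproduce. The check has four steps.

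**Inputs from the protocol article.** Horizon 24 weeks, so at most 24/52 = 0.46 QALY per person. Sample size 91 per group before the dropout allowance and 108 per group planned (Sample size justification).

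**Assumptions, not in the document.** Utility SD 0.15 to 0.25; sustained utility gain 0 to 0.08; willingness to pay λ = $50,000 per QALY. For step 3, mean control cost $3,000, cost SD $5,000 and utility SD 0.20. For step 4, the values given there.

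**1. Sign ambiguity.** Ratio = ΔCost/ΔQALY. Net monetary benefit (NMB) = λ × ΔQALY − ΔCost.

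| Case | ΔCost | ΔQALY | Ratio | NMB at $50,000 |
|---|---|---|---|---|
| Dominant | −500 | +0.01 | −50,000 | 500 + 500 = +1,000 |
| Dominated | +500 | −0.01 | −50,000 | −500 − 500 = −1,000 |

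Since (−ΔCost)/(−ΔQALY) = ΔCost/ΔQALY, reversing the sign of both differences in every replicate leaves the ratio's distribution, and so its interval, unchanged. No assumed SD is involved.

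**2. How often replicates cross zero.** SE(ΔQALY) = SD × (24/52) × √(2/n). With SD 0.20 and n = 91: 0.20 × 0.4615 × 0.1482 = 0.0137. For a trial whose observed utility difference is d, the share of replicates below zero is about Φ(−d × 0.4615/SE).

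| Utility difference (n = 91) | SD 0.15 | SD 0.20 | SD 0.25 |
|---|---|---|---|
| 0 | 50% | 50% | 50% |
| 0.02 | 18% | 25% | 30% |
| 0.04 | 4% | 9% | 14% |
| 0.06 | 0.3% | 2% | 5% |
| 0.08 | <0.1% | 0.3% | 1.5% |

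With 108 per group the shares are a little lower (16% to 28% at 0.02; 2.5% to 12% at 0.04).

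**3. Width of the ratio interval.** Percentile bootstrap, 400 simulated trials per scenario, 1,000 replicates each, n = 91, cost differences of ±$500.

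| True ΔQALY | Median width, $ per QALY |
|---|---|
| 0.005 | about 1.3 million |
| ±0.02 | about 0.63 to 0.75 million |
| 0.04 | about 0.11 million |

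The ratio interval still covered the true ratio in about 96% to 99% of these trials. The fault is therefore not under-coverage: the interval is correct for a quantity that cannot be read. The NMB interval covered its target in 93% to 95%.

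**4. What the acceptability curve adds.** Take a cloud of replicates with ΔCost of mean −500 and SD 400, and ΔQALY of mean 0.01 and SD 0.0137, then its mirror image. Both give the same 95% ratio interval, about −$542,000 to +$446,000. The acceptability curve at $50,000 reads 0.90 for the first and 0.10 for the second.

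**The case against.** The strongest reply is that the plan does not rest on the ratio alone. The acceptability curve gives, at each threshold, the probability that net benefit is positive. It separates dominant from dominated results, stays defined when the QALY difference is zero, and speaks directly to research question 3. This stands. A reader might infer that the economic analysis answers the wrong question altogether; with the curve in the same section, the document does not support that.

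A reader might also infer that the plan would pass off a harmful, dearer programme as cost-effective. In simulations with −0.03 QALY and +$1,500 (86 to 108 per arm, QALY SD 0.05 to 0.08, cost SD $1,500 to $4,000, all assumed), the ratio interval lay wholly below $50,000 in 68% to 99% of trials. But the document has no rule that declares success when the ratio's upper limit is under a threshold, and the median acceptability-curve probability at $50,000 was 0.00 in every such setting. Those percentages are error rates of a rule that the plan does not contain.

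Nor does the document show that near-zero QALY differences will be the usual case. It gives no QALY SD, cost SD or expected QALY gain. The 0.46 ceiling limits the spread of QALYs as well as the difference, so it does not by itself make the difference small against its standard error.

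Finally, an article may leave quadrant rules, separate increments and threshold values to the full plan. That is fair for those details. It does not cover the interval on the ratio, which the article itself prescribes.

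**Conclusion.** The point holds in a limited form. Followed as written, the plan puts a 95% CI on a ratio that cannot distinguish a dominant from a dominated programme, under a hypothesis that predicts dominance. That part is algebraic and needs no assumption.

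The second part, an interval too wide to use, is plausible but conditional. Under the assumed SDs it is material at sustained utility gains of about 0.02 to 0.04 and largely gone at 0.06 to 0.08.

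The defect is confined to the main ratio and its CI; the acceptability curve is sound. Severity is minor, because cost-effectiveness is a tertiary objective and a valid measure of decision uncertainty is already planned.

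**What to change.** Amend the Cost-effectiveness analysis section so that the same bootstrap replicates yield, for both the public payer and the societal perspective:

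- incremental cost and incremental QALYs, each with a 95% CI;
- incremental net monetary benefit with its 95% CI at one or two willingness-to-pay values stated in advance;
- the ratio as a point value only where it is interpretable, with 'dominant' or 'dominated' stated otherwise;
- no CI on the ratio when replicates span quadrants;
- the acceptability curve, as already planned.

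This is a change of wording. It needs no new data and no further resampling. Its one cost is that the investigators must name the willingness-to-pay values before seeing the results.

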### Feasibility

The results of the pilot provided us with information about the feasibility of the project including the recruitment, randomization, the ability of this population to undertake and remain safely engaged in the program, and the suitability and responsiveness of the outcomes.

### Protocol modifications

We will communicate any changes to the study protocol to study investigators and the Hamilton Integrated Research Ethics Board and other research ethics boards (in writing) and electronically to the trial registry (www.clinicaltrials.gov). Participants will be contacted by phone to communicate any change in risk.

## Discussion

This proposed study will be the largest RCT examining the effectiveness of a community program for individuals with stroke. Additionally, as a RCT with broad study eligibility criteria, participants in the study will represent a wide spectrum of individuals living in the community with stroke, reflecting the heterogeneity of this population. Thus, if positive benefits are demonstrated, results will provide strong research evidence to support the implementation of structured, community-based exercise and education programs for a broad range of people living in the community with stroke. However, the rate of change is likely to be diverse, due to the wide age range and length of time since stroke, and this may limit the effect of the intervention. The advantage of the broad eligibility criteria is the generalizability of the results. We have expertise within our team to support the implementation of FIT for FUNCTION in communities from diverse regions; as a result of the pilot study, we developed strategies to address these challenges.

The eligibility, as noted, for this trial are very broad so there will be a heterogeneous sample of participants with a wide range of function, fitness, and ages who will potentially participate. This approach was intentional as this will be the target population who will receive the intervention through the YMCAs if it is a positive trial. However, this broad sampling approach may diminish the effect size. Although the participants of the trial need to gain medical clearance to participate, referral occurs by self-referral or by a health practitioner. This may result in some degree of sampling bias since this approach may self-select people who have had a previous propensity for exercise and engagement in positive health behaviors. Attrition maybe a factor due to age, reoccurrence of stroke, or other health issues. Absenteeism is often seasonal in this age group, where attendance rates may drop in the winter months when travel becomes increasingly challenging. Depression is often associated with stroke and may result in difficulties for participants remaining in the trial. Since participants are required to have completed bloodwork before having their baseline assessment and randomization, it is possible that persons who would usually join an exercise trial but who would not wish to undertake bloodwork will exclude themselves.

A limitation of the trial, as with most rehabilitation trials, is that it is not possible to blind the participants. Therefore, participants who are randomized to the control group may find it more difficult to adhere to exercise where there is less standardization and support compared to the intervention group. In addition, expanding this intervention to other YMCAs that have their own institutional idiosyncrasies may result in some site-specific effects, so we plan to examine the results of the trial by site. A further consideration is how time since stroke may influence the primary outcome of reintegration and may introduce bias. Persons who have low reintegration scores at one year, for example, may be different from participants with stroke who have low scores at 30–60 days which would result in the population at risk being different at the assessment time points. Persons who enter the trial at shorter time post stroke may have more spontaneous improvement and reintegrate earlier biasing the comparison to the null while persons who enter later may have more severe disease which will decrease the likelihood of a response in either group. To address this issue, we will adjust for time since stroke in our analyses and also use time since stroke to create subgroups to examine the outcomes.

A novel aspect of this study is it will be the first community-based trial to examine exercise-associated changes to cardiovascular risk factors. Despite the known increase in risk for recurrent events [4], cardiovascular risk factors are often poorly managed after stroke [13, 66]. The benefits of fitness training on walking ability are clearly established [102] but there is insufficient evidence that analogous improvements in cardiovascular risk factors can be observed. Few studies have included risk factors as outcomes and most have been conducted in research settings or in other controlled environments with smaller sample sizes. This study offers a large sample size to contribute to the state of the evidence related to changes in these risk factors following exercise and is the first community exercise trial to inform how to implement such strategies for secondary prevention within a sustainable community program model.

Ultimately, the results will help to inform how healthcare institutions and community agencies can work together to provide long-term exercise to persons of all ages following stroke and will increase the understanding about the degree of support and tailoring required to make these programs effective. It will also provide the foundation for future studies using factorial designs to more specifically examine effects of dosage and exercise types.

Another key innovation of the FIT for FUNCTION program is that it involves a unique and innovative collaboration through the LiveWell partners across healthcare, community, and academic centers. Our partners and collaborators include those who provide service delivery, those who coordinate regional stroke services, and from the Local Health Integrated Network who manage the overall integration of healthcare services. The YMCA delivers recreational services in all provinces and regions across Canada. This partnership will ensure that, if the results are positive, this model of care will be disseminated provincially and nationally within their organization and to other service providers. Each province and territory has a Stroke System and the YMCA is a national body, which will ensure that the impact from this trial is high.

### Anticipated results and research knowledge translation strategies

Results will be disseminated through professional organizations, the Ontario Ministry of Health and Long-Term Care, peer review conferences, journal articles, and special interest groups such as local and regional stroke recovery groups. Provincially, the Principal Investigators, Co-Investigators, Knowledge Users, and Collaborators on this current proposal will provide support and networking through Regional, Provincial, and National Stroke Networks such as the Heart and Stroke Foundation of Canada for other groups who wish to develop similar programs within their communities. The project results will be communicated at provincial and national stroke forums such as: The Annual Stroke Symposium Meeting of the Inter-Urban Stroke Academic Association; the Annual Stroke Collaborative; and the Canadian Stroke Congress. The LiveWell model and the study results will be also be disseminated provincially and nationally within the YMCA organization to stakeholders (healthcare professionals, healthcare administrators, and policy makers) from different provinces and territories.

## Trial status

Recruitment started in October 2014 and at the time of protocol submission, this study is recruiting participants. Recruitment is anticipated to be completed by December 2017.

## Abbreviations

6MWT: 6-min walk test
BBS: Berg Balance Scale
BP: Blood pressure
CRF: Case report form
CVD: Cardiovascular disease
EQ-5D-5L: European Quality of Life 5-Dimension Questionnaire
HR: Heart rate
ICF: International Classification of Functioning, Disability and Health
LRC: Lead research coordinator
LWS: Living with Stroke
MoCA: Montreal Cognitive Assessment
PAM: Patient activation measure
QALY: Quality-adjusted life year
RAPA: Rapid Assessment of Physical Activity
RCT: Randomized controlled trial
RNLI: Reintegration to Normal Living Index
SE: Self-efficacy
SPPB: Short Physical Performance Battery
